### Interrupted Time Series

ITS using segmented regression has several strengths over the pre-post study design. It controls for secular trends over time, provides powerful, easy to understand visual outputs, and may improve generalisability to the wider population
^7,
8,
19^. For this study, data are available to evaluate both policies described above in an ITS analysis.

The two interventions in this study were introduced at specific, well defined time points, allowing for clear separation of pre- and post-intervention periods.
Figure 1 provides a timeline for the interventions in questions and
Table 3 provides details of the planned analyses and time periods included in each. As shown in
Figure 1, the same 12-month time period is used for both ITS analyses meaning they are not independent. However, there is insufficient time or data points to prevent this overlap, and this will be discussed as a potential limitation of the study.

**Table 3. T3:** Planned ITS analyses.

Policy change	Dates	Analyses
Change in TXA dose policy	Pre-intervention 01/11/2008 – 31/07/2011 Excluded implementation (lag) period 01/08/2011 – 31/01/2012 Post-intervention * 01/02/2012 – 31/01/2013	PRIMARY – Population-level effects of TXA policy for all patients undergoing THR or TKR
Introduction of preoperative anaemia screening programme	Pre-intervention * 01/02/2012 – 31/01/2013 Excluded implementation (lag) period 01/02/2013 – 31/07/2013 Post-intervention 01/08/2013 – 31/07/2014 (sensitivity analysis 01/08/2013 – 28/02/2019)	PRIMARY – Population-level effects of anaemia screening programme for ***all patients*** undergoing THR or TKR (with equal number of data points pre- and post-intervention)
		SECONDARY - Effect on anaemic subpopulation ***eligible for any*** ***treatment*** as per anaemia pathway (Hb <120g/L, female or 130g/L, male) **, modelled against non-anaemic cohort
		SECONDARY - Effect on anaemic subpopulation ***eligible for iron*** treatment only (Hb 105–119g/L female, 115–129g/L male & ferritin 12- 100), modelled against non-anaemic cohort (excluding those with Hb <105 or <115 and those referred to GP/haematologist).
		SECONDARY - Effect on anaemic subpopulation ***given iron*** treatment only (as above but only those given iron), modelled against non-anaemic cohort (same exclusion as above) – per protocol analysis

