* Post-intervention period for TXA policy is the same as the pre-intervention period for anaemia screening programme analysis. **includes GP referral, haematology referral or any form of iron

An early step in ITS analysis is to generate summary statistics for each time period and undertake simple pre-post comparisons
^20^. This will be performed in this study and later compared to the results from ITS and RDD analyses.

***Data description.*** ITS is said to work best with short-term outcomes that change quickly after implementation of an intervention or after a clearly defined lag period
^8^. This study is examining short-term outcomes; however, some delays to observed changes in outcomes after policy implementation are expected. The orthopaedic department has previously reported that a 6-month lag period was required to fully adopt the increased TXA dose policy
^16^. This same lag will therefore be incorporated into this ITS analysis. Regarding the introduction of the preoperative anaemia screening programme, staff running the anaemia service report that this started promptly on 01/02/2013, after detailed planning, and uptake was rapid. However, a lag to observed changes in outcomes will be inevitable due to surgical waiting list times. Comparing screening and surgery dates for the first 10 anaemic and 10 non-anaemic patients from the cohort shows all but one had their surgery within 6 months of screening. Therefore, a 6-month implementation (lag) period is also considered appropriate following introduction of the anaemia screening service (
Figure 1). Lag periods will be accounted for by excluding this data from the primary analysis
^21^. As individual procedure-level data are available, including data indicating whether or not anaemia screening was received, an alternative approach to handling the lag period for the analysis of the anaemia screening programme, could be to model the intervention as a continuous implementation variable ranging from 0 to 1, instead of as a binary (0/1) variable. This would allow the effect of the intervention to be modelled as a weighted average during the 6-month implementation period, which could be a more efficient use of the data available. A sensitivity analysis of this alternative method for handling the 6-month implementation period will be included in this study.

ITS requires sequential measures of the outcome, at regular intervals, before and after the intervention time points
^20,

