21^. In keeping with many ITS studies, individual-level outcome data will be converted to, and presented as, proportions or means at monthly intervals and a segmented-regression analysis performed
^21^. ITS plots will be generated and visually inspected to determine if linear or non-linear regression modelling is appropriate. A minimum of 8 data points pre- and post-intervention are desirable
^20,
21^. It is expected the shortest time frame being analysed in this study will include 12 months/data points, thus surpassing this requirement. The power of an ITS analysis is increased if there are an equal number of data points pre- and post-intervention
^22^. In the case of preoperative anaemia screening there are expected to be 12 data points in the pre-intervention period but 60 in the post-intervention period. As such, to increase power of this analysis this period will be cut to include only 12 time points, after the 6 month lag period, for the primary analysis of the anaemia screening policy. Sensitivity analysis including all post-implementation data points will be conducted.

***Addressing threats to validity.*** Time varying confounders are the main threat to the validity of ITS studies
^21^. These are specific to each ITS study and are carefully considered later in this SAP. However, the most robust way to account for time varying confounders, even those that are unknown, is to model against a control group. This could either be a different population not exposed to the intervention or, if individual-level data are available, by splitting the data into two groups, one group targeted by an intervention and another that is not. In this study, data for a different group of patients is not available for either intervention. The TXA policy is targeted at all THR or TKR patients so this data cannot be split. However, the anaemia screening policy targets a specific subgroup of anaemic patients with treatments so the population can be split into two groups to increase the robustness of this analysis. As such the two interventions will be modelled separately: 1) the TXA intervention without a control group, and 2) the anaemia screening intervention with a control group.

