***Developing the model.*** Data will be inspected for outlier data points and, where identified, explanations will be sought and exclusion considered. First order lagged residuals will be included in the ITS models to account for autocorrelation
^20,
25^. The use of 6-month implementation periods in this study could be the same time between the lowest and highest points in an annual cycle, should seasonality affect outcomes. Although this is not expected in this instance, a sensitivity analysis including a lag of 12 time points (assuming seasonality) will be undertaken to test the robustness of the two primary analyses.

***Sensitivity analysis.*** An optimal model will be developed and described for these ITS analyses. The impact of decisions taken during this process such as inclusion/exclusion of outlying data points and autocorrelation adjustments will be tested in sensitivity analyses. Further analyses of data stratified by surgery type (THR or TKR) and/or by patient gender, will be conducted if data permits, as these may impact on outcomes.

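### The lag-12 seasonality check cannot test annual seasonality in the anaemia primary ITS: the 12-point lag uses up the whole pre-intervention period and pairs opposite seasons

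*SAP article*

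**What the plan says.** Under Interrupted Time Series, the SAP article fixes the following.

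- Outcomes are analysed as "proportions or means at monthly intervals and a segmented-regression analysis performed".
- For the anaemia primary analysis, Table 3 gives "Pre-intervention * 01/02/2012 – 31/01/2013", then "Excluded implementation (lag) period 01/02/2013 – 31/07/2013", then "Post-intervention 01/08/2013 – 31/07/2014". The text under Data description confirms the length: "this period will be cut to include only 12 time points, after the 6 month lag period, for the primary analysis of the anaemia screening".
- The implementation months are dropped: "Lag periods will be accounted for by excluding this data from the primary analysis".
- Under Developing the model: "First order lagged residuals will be included in the ITS models to account for autocorrelation".
- The same paragraph says that a 6-month gap could coincide with half an annual cycle. Seasonality is not expected, but "a sensitivity analysis including a lag of 12 time points (assuming seasonality) will be undertaken to test the robustness of the two primary analyses".

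The article does not say whether the 12 points are counted over retained rows or calendar months. Nor does it say what happens to rows that have no lagged value.

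**The concern.** The authors have identified a real weakness of their design. If transfusion rates vary with the season, removing half a year at the interruption can look like a level or slope change. They chose the lag-12 term to test for this.

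A lag of 12 points needs 12 earlier points, and the anaemia pre-intervention period is exactly 12 points long. Deleting six months also means that 12 retained points no longer span a year. The check named for the study's primary aim may therefore give no estimate, or give one that says nothing about annual seasonality, while being reported as a robustness result. The all-patient anaemia primary analysis has no control group in the model to absorb a seasonal pattern.

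**Working it through.** **Inputs (Table 3, counted in calendar months)**

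| Series | Pre | Excluded | Post | Retained |
|---|---|---|---|---|
| Anaemia primary | Feb 2012–Jan 2013 = 12 | Feb–Jul 2013 = 6 | Aug 2013–Jul 2014 = 12 | 24 |
| TXA primary | Nov 2008–Jul 2011 = 33 | Aug 2011–Jan 2012 = 6 | Feb 2012–Jan 2013 = 12 | 45 |

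The 12 + 12 count agrees with the article's own.

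**Model.** y = b0 + b1·time + b2·post + b3·post·(time − first post month), plus the lagged residual, fitted to rows where that residual exists. Time is in calendar months.

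**Step 1: which rows have a lag-12 value, counted over retained points?**

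- Anaemia: 24 − 12 = 12 rows. The first pair is Aug 2013 with Feb 2012, and the last is Jul 2014 with Jan 2013. All 12 rows are post-intervention and none is pre-intervention.
- TXA: 45 − 12 = 33 rows, of which 33 − 12 = 21 are pre-intervention and 12 are post-intervention.

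**Step 2: calendar distance of the pairs.** A pair that crosses the deleted gap is 12 + 6 = 18 months apart.

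- Anaemia: all 12 pairs are at 18 months. An annual cosine has correlation −1 across them.
- TXA: 21 pairs are at 12 months (all pre-intervention) and 12 are at 18 months (every post-intervention row).

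**Step 3: estimability.** With only post-intervention rows, the post indicator equals the intercept column, and post·(time − first post month) is a linear function of time and the intercept.

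- Anaemia: the four segmented-regression columns fall from rank 4 to rank 2 (3 of 5 with the lag term). Neither b2 nor b3 is estimable.
- TXA: rank 5 of 5, so both are estimable.
- Anaemia with the long post-intervention period: the first 12 points are still the whole pre-period, so the rank is again 3 of 5.

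**Step 4: does a true 12-calendar-month lag rescue it?** For anaemia only Aug 2013–Jan 2014 can be paired (with Aug 2012–Jan 2013). That gives 6 rows, all post-intervention, rank 3 of 5, still not estimable.

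**Step 5: the first-order lag at the join.** If the gap is closed, Aug 2013 is paired with Jan 2013, which is 7 months earlier. This affects one row per series.

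**Step 6: how much could seasonality matter?** Regress A·cos(2πt/12 − φ) on the four segmented columns and take the maximum over φ, that is, the square root of the summed squared coefficients for the cosine and sine parts. A is half the peak-to-trough difference. The mid-post effect is b2 + 5.5·b3.

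| | Level change at first post month | Mid-post effect |
|---|---|---|
| Anaemia (12 + gap + 12) | 1.13A | 1.13A + 5.5 × 0.324A = 2.92A |
| TXA (33 + gap + 12) | 0.60A | 0.49A |

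If time is instead renumbered across the gap, the anaemia figures are about 0.2A and 1.9A.

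**Step 7: would a sine/cosine pair work?** Adding cos(2πt/12) and sin(2πt/12) gives rank 6 of 6 on the 24 anaemia points, with 24 − 6 = 18 residual degrees of freedom. Standard errors come from the diagonal of (X′X)⁻¹, in units of the residual standard deviation sigma, assuming independent errors.

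| SE | Without pair | With pair |
|---|---|---|
| Anaemia level change | 1.21 | 1.33 |
| Anaemia slope change | 0.118 | 0.193 |
| TXA level change | 0.71 | 0.72 |

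**The case against.** **Failure depends on the implementation.** The article does not say that rows without a lag are dropped. A maximum-likelihood error model with a lag-12 term does converge on 24 points. This stands as a limit on saying that nothing can be computed. It does not rescue the check: over retained points the fit uses only 18-month pairs, over calendar months it rests on 6 pairs, and a full AR(12) spends 17 parameters on 24 points.

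**The word lag also names the implementation period.** The sentence might mean a 12-month exclusion. That fits poorly, because TXA would keep only Aug 2012–Jan 2013. Those 6 points are below the article's desirable minimum of 8 and its stated shortest segment of 12.

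**A reader might infer that the study has no protection against a seasonal artefact.** The article does not support that.

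- The planned simple pre-post comparison for anaemia sets one complete year against another, so a stable annual cycle cancels from the mean monthly rates.
- The controlled secondary analyses remove seasonality shared by anaemic and non-anaemic patients.
- The graded 0-to-1 implementation sensitivity analysis keeps the gap months.
- The regression discontinuity does not use time as its assignment variable.

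None of these is a seasonality term in the primary model, but together they give partial protection.

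**A reader might also infer that the TXA check fails in the same way.** It does not. It can be fitted, 21 of its 33 pairs are true 12-month pairs, and its worst-case bias is much smaller. What remains is that all 12 post-intervention rows carry an opposite-season lag.

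**Seasonality is not expected, and this is only a sensitivity analysis.** Both are true, and they limit the severity.

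**Conclusion.** The point holds for the anaemia primary ITS. With lagged residuals in the model and the gap months excluded, as the article states, the lag-12 check leaves 12 rows, all post-intervention and all paired at 18 months, and it gives no estimate of the level or slope change. Calendar indexing leaves 6 rows and the same result. Other fitting methods return a number but do not meaningfully test annual seasonality. For TXA the check runs, but it mixes 21 pairs at 12 months with 12 at 18.

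The seasonal biases (anaemia up to about 1.1A and 2.9A, TXA about 0.6A and 0.5A) assume a pure annual cycle, calendar-time coding and the least favourable phase. A is not given, so they show sensitivity and do not predict an error. The documents do not show that the primary estimates are biased, and no primary estimand or test changes.

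This should be fixed, because a pre-specified robustness check for the primary aim cannot do what it is meant to do.

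**What to change.** In the seasonality sensitivity analysis, replace the 12-point lag with one annual sine/cosine pair indexed by calendar month, fitted in each of the two existing primary series. State that residual lags, including the first-order lag, are indexed by calendar month, with excluded months treated as missing so that the series is not closed up over them.

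The cost is a sentence or two in the SAP and a few lines of R. In precision, the anaemia level-change SE rises by about 10% (1.33/1.21 = 1.10) and the slope-change SE by about 64% (0.193/0.118 = 1.64). The TXA level-change SE rises by little more than 1% (0.72/0.71). The slope cost is real, but it falls only on the sensitivity analysis.

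One model over the whole series would identify season from more cycles. It is optional, since the article deliberately models the two interventions separately and such a model assumes one seasonal pattern throughout. The Study status section says that analysis awaits publication of the plan, so the change can be made before results are seen.

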### Regression discontinuity

RDD estimates the local average treatment effect when treatment decisions are based around a cut-off value for a continuous variable
^26^. For example, giving iron (the treatment) with the intention of reducing RBC transfusion and LoS (the outcomes) to patients whose Hb (the assignment variable) falls below a pre-defined cut-off of 120g/L for females or 130 g/L for males (the threshold). RDD makes use of this threshold and assumes that individuals who lie just above it belong to the same populations those who lie just below it, and assignment to treatment or not is considered random
^27^.

The main strength of RDD lies in its ability to achieve a balance of unobserved factors in patients that fall, by chance, either side of the threshold value, much like a RCT
^28^. The local nature of the effect examined in RDD can also be used in optimising threshold levels. In this case we may be able to examine if a threshold Hb of 120 or 130g/L may be more appropriate for females, as is being suggested in some studies
^12,
28–
30^. As the TXA policy affects all patients it is only possible to conduct a RDD analysis for the anaemia screening programme, using data since the inception of this programme (1
^st^ February 2013,
Figure 1).

***Data description.*** In this study the continuous assignment variable will be preoperative Hb concentration. The outcome assessment, for primary and secondary outcomes (listed above), are observed universally for patients who receive treatment or not. Details of how treatment is assigned has been previously reported, and is shown in
Figure 2
^17^. Notably the treatment thresholds are different for males (Hb 130g/L) and females (120g/L), so data will be stratified by gender for analysis. The treatment thresholds are based on World Health Organisation definitions for anaemia
^31^.

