## Abstract

Perioperative blood transfusion is associated with poorer postoperative outcomes following hip and knee replacement surgery. Evidence for the effectiveness of some measures aimed at reducing blood transfusions in this setting are limited and often rely on weak pre-post study designs. Quasi-experimental study designs such as interrupted time series (ITS) and regression discontinuity design (RDD) address many of the weaknesses of the pre-post study design. In addition,
*a priori *publication of statistical analysis plans for such studies increases their transparency and likely validity, as readers are able to distinguish between pre-planned and exploratory analyses. As such, this article, written prospective of any analysis, provides the statistical analysis plan for an ITS and RDD study based on a data set of 20,772 primary elective hip and knee replacement patients in a single English NHS Trust. The primary aim is to evaluate the impact of a preoperative anaemia optimisation service on perioperative blood transfusion (within 7 days of surgery) using both ITS and RDD methods. A secondary aim is to evaluate the impact of a policy of increased tranexamic acid dose given at the time of surgery, using ITS methods.

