**Figure 1. f1:**
[figure not shown]
Timeline of patient blood management interventions introduced at Northumbria NHS Foundation Trust and data for analyses. ERP = Enhanced Recovery Programme IV = Intravenous, TXA = Tranexamic acid, ITS = interrupted time series, RDD = regression discontinuity design.

As part of on-going service evaluation, a large dataset of 20,772 primary, elective THR or TKR procedures performed at NHCT has been compiled. Procedures included in this dataset are those recorded with a procedure code (OPCS4) related to a primary hip or knee replacement, as detailed in
Table 2. Procedures recorded with any other OPCS code are excluded from this dataset. The number of procedures included with each OPCS code will be reported with the results of this study.

**Table 2. T2:** Procedure codes (OPCS-4) included in the dataset for this study.

OPCS code	Description
W371	Primary total prosthetic replacement of hip joint using cement
W381	Primary total prosthetic replacement of hip joint not using cement
W391	Primary total prosthetic replacement of hip joint NEC
W401	Primary total prosthetic replacement of knee joint using cement
W411	Primary total prosthetic replacement of knee joint not using cement
W421	Primary total prosthetic replacement of knee joint NEC

This includes data from hospital electronic record systems, such as the Patient Administration System and Blood Transfusion database, and a prospectively maintained database for the pre-operative anaemia screening service. The dataset includes patient demographics, comorbidities, pre-operative anaemia screening results (i.e. haemoglobin concentration, Hb), anaemia treatment given, operative details, post-operative complications, blood transfusions and length of hospital stay (LoS). The full dataset covers a time period from January 2008 to March 2019.

Ethical approval was not required as this is a retrospective study of routinely collected data. Local Caldicott guardian approval was given for use of these data. Data flow will be presented in a STROBE diagram in the resulting publication
^18^. Population characteristics (age, gender, comorbidities, type of surgery) and descriptive statistics will be presented in tables for the cohorts being studied. Analyses will be performed using R and RStudio (version R-3.6.2 for mac, R Core Team 2013,

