http://www.R-project.org/) on an intention to treat basis, and per protocol where possible. Results will be presented in terms of absolute and relative values with 95% confidence intervals where appropriate. Results will be considered statistically significant if the p-value ≤0.05.

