### Outcomes

The primary outcome is the proportion of procedures requiring perioperative allogenic RBC transfusion (within 7 days of surgery). Secondary outcomes are the quantity of blood transfused per procedure (RBC units), LoS per procedure (in days), critical care admission rate per 100 procedure (within 30 days post-surgery) and emergency readmission rate per 100 procedures (within 30 days post-surgery)
^1,
2,
17^.

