^28^. If differences are seen, and it is possible the more anaemic patients (lower Hb) have more comorbidities and/or are older, then variables which are identified as being different between the two groups will be included as covariates in the final model. Similar to ITS, RDD is sensitive to co-interventions introduced around the threshold Hb value. There are no known co-interventions introduced locally for this patient cohort around the threshold Hb values.

***Developing the model.*** In graphical representations of the data, Hb will be divided into bins. Outcome data for this study is in the form of discrete variables (yes/no: transfused / readmitted / critical care admission; and number of inpatient days). As such, outcome data will be converted to a probability (i.e. risk of transfusion) or average (i.e. mean number of days) for each bin. To decide optimal bin size, plots of Hb and primary outcome (transfusion rate) will be generated for a range of bin sizes (i.e. 1, 2 or 5 g/L). Visual inspection of these plots will be used to rule out bin sizes that are clearly too wide or too narrow. For the remaining bin sizes, F-tests using
*k*2 dummies and interactions will be performed to identify bin sizes that do not over smooth the data. From the remaining choices the widest bin size that is not rejected by either F-test will be chosen
^32^. The same bin size as chosen for the primary outcome will be used for plotting other outcomes to facilitate comparison. 95% confidence intervals will be plotted alongside the probabilities or averages where applicable.

Separate scatter plots of primary and secondary outcomes against Hb will be created. These will be inspected visually for a jump at the threshold value, indicative of a treatment effect. Data will be inspected for outlying data points and consideration given to exclusion. Sensitivity analysis with and without outlying data points will be performed.

As the sample size for this analysis is relatively small a parametric estimation of treatment effect will be used for the primary analysis using logistic regression
^32^. Length of stay will be considered as a continuous outcome. The F-test will be used to determine the optimal functional form of the parametric regression model. Starting with a simple linear model, a higher order term will be added to the model until the F-test is no longer statistically significant
^32^.

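### The regression discontinuity analysis is stratified by sex because the Hb cut-offs differ, but no overall estimate is planned for the primary aim it serves

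*SAP article*

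**What the plan says.** - The Abstract of the SAP article states that the primary aim, the effect of the anaemia service on perioperative transfusion, is evaluated "using both ITS and RDD methods".
- Under Regression discontinuity, Data description, the analysis is split by sex: "Notably the treatment thresholds are different for males (Hb 130g/L) and females (120g/L), so data will be stratified by gender for analysis".
- Under Developing the model in the same section: "As the sample size for this analysis is relatively small a parametric estimation of treatment effect will be used for the primary analysis". No RDD sample size, power or effect size is given.
- Under Data source: "Results will be considered statistically significant if the p-value ≤0.05". There is no rule for reading several results together.
- For the interrupted time series (ITS), Table 3 makes the primary analysis of the anaemia programme one of all patients together. Stratification by sex appears only as a further analysis under Sensitivity analysis.

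The RDD section does not centre Hb on the sex-specific cut-off, plan a pooled jump, combine the two sex-specific estimates, or say how two results will answer the primary aim.

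**The concern.** The stated reason for splitting does not rule out an overall result. The assignment variable can be redefined as Hb minus the patient's own threshold, which puts both sexes on one scale with the cut-off at zero. Sex and sex-by-Hb terms on each side then let men and women keep their own curves, so only the jump is shared.

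Two things are at stake. First, precision: the plan names a small sample as the constraint that drives its choice of a parametric model, yet provides for no estimate that uses the whole sample. Second, interpretation: two less precise results can differ by chance, and nothing says what would then be concluded. The ITS section also promises to compare the simple pre-post results with those from ITS and RDD, and the RDD offers no all-patient figure for that comparison.

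**Working it through.** The plan states no figure for RDD size or precision, so there is none to reproduce. The check sets the precision of each sex-specific estimate against that of a combined one.

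**Approximate volume (context only).** Data source reports "a large dataset of 20,772 primary, elective THR or TKR procedures performed at NHCT has been compiled", and "The full dataset covers a time period from January 2008 to March 2019", which is 135 months if both end months are complete. The RDD starts on 1 February 2013, so it covers 74 months to March 2019.
- At the plan's expected 100 procedures a month: 100 × 74 = 7,400.
- At the dataset average: 20,772 / 135 = 153.9 a month, and 153.9 × 74 ≈ 11,400.

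Both assume constant volume and an Hb value for every procedure. The plan does not give the division by sex.

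**Standard errors.** The two sexes share no patients, so their estimates are independent and information adds. If one sex carries a share f of the information, then SE(combined) = SE(that sex) × √f.

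| Information split | √f | Combined SE is smaller by |
|---|---|---|
| 50:50 | 0.707, 0.707 | 29%, 29% |
| 60:40 | 0.775, 0.632 | 23%, 37% |

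**Power, for illustration.** Take a combined analysis with 80% power and the same true effect in both sexes. Single-sex power is Φ[(1.960 + 0.842)√f − 1.960].
- 50:50: 2.802 × 0.707 − 1.960 = 0.021, giving 51% for each sex.
- 60:40: 2.802 × 0.775 − 1.960 = 0.21, giving 58%; and 2.802 × 0.632 − 1.960 = −0.19, giving about 43%.

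At 50:50, both sexes reach p ≤ 0.05 with probability 0.508² = 0.26, and exactly one does with probability 2 × 0.508 × 0.492 = 0.50. At 60:40 the figures are 0.25 and 0.51. A split result would therefore be the most likely outcome even with no true difference between the sexes.

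**Simulation of the two ways to combine.** Assumptions: 10,000 procedures, 58% women, Hb mean 131 (SD 12) in women and 143 (SD 13) in men, a logistic model and a common jump of −0.4 on the log-odds scale. Mean standard errors of the jump over 60 simulated datasets:

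| Analysis | SE |
|---|---|
| Women only | 0.240 |
| Men only | 0.308 |
| One model, centred Hb, sex-specific slopes, common jump | 0.188 |
| Inverse-variance combination of the two sexes | 0.189 |

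The last row is 1/√(1/0.240² + 1/0.308²) = 0.189. The two routes are equivalent for practical purposes.

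**The case against.** The strongest reply is that stratified fitting is sound, and much of it stands. An RDD estimates a local effect, and the effects at 120 g/L in women and 130 g/L in men are different quantities. Centring aligns the cut-offs but not the baseline risk of transfusion, so a common jump is an added assumption. The section also raises the question of which threshold suits women, and that needs a women-only model. The plan's choice to fit by sex is therefore not an error in itself.

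Several stronger readings are tempting and are not supported.
- **That the plan sets up two primary answers and excludes a combined one.** The text only says that data will be stratified. It labels no pair of primary results; the gap is inferred from the absence of any combining step.
- **That the primary aim has no overall estimate.** The primary ITS gives one for all patients. The gap is confined to the RDD.
- **That the split halves a sample already called small.** The sex split is not stated, and the remark about sample size may already refer to the sex-specific samples.
- **That false positives rise to 9.75%** (1 − 0.95²). This needs a rule by which success in either sex would be claimed, and the plan has no such rule.
- **That precision is irrecoverably lost.** The simulation shows that combining the two stratified fits recovers essentially all of it.

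What the reply does not answer is that the plan, followed as written, ends with two less precise estimates and no stated way to bring them together.

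**Conclusion.** The point holds as a gap in the planned RDD result, not as an objection to sex-specific analysis. Differing cut-offs explain why Hb cannot be pooled on its raw scale; they do not explain why no overall estimate is planned for a method that serves the primary aim. A combined estimate would have a standard error about 29% smaller than either single-sex one at equal information, or 23% and 37% smaller at 60:40. These shares are assumptions. The power and simulation figures are relative illustrations, since the plan gives no RDD effect size, event rate or sex split. The change is worth making before analysis begins.

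**What to change.** Keep the sex-specific RDDs, and add one pre-specified overall RDD estimate for the primary outcome. Choose one of two forms in advance:

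1. one logistic model on Hb minus the sex-specific threshold, with sex and sex-by-Hb terms on each side of zero and a common jump; or
2. an inverse-variance combination of the two sex-specific jumps on the log-odds scale, which leaves the plan's model-building within each sex unchanged.

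Report it with a sex-by-jump interaction, so that a difference between the sexes is tested directly and not judged by comparing two p-values. State that this overall estimate is the RDD result that answers the primary aim.

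The cost is wording only: Study status says the analysis is still pending, and no further data are needed. The downside is that the overall estimate is a sex-averaged local effect and assumes a broadly common jump. The interaction and the retained sex-specific results show whether that is reasonable. Neither clinical threshold is touched.
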